### Interim analyses {21b}

An interim analysis of adverse side effects will be conducted during the study. Once 42 patients, representing half of the planned study population, in each group, have completed the 6-month follow-up, the research team will assess the incidence of neuropathic pain. This assessment will be conducted using the DN4 questionnaire. A potential neuroma is considered present if a patient scores ≥4 on the DN4. If *a* ≥ 400% difference is observed in the proportion of patients scoring ≥4 on the DN4 questionnaire between the treatment groups, the study will be terminated due to an unacceptably high incidence of neuropathic side effects. Assessments of function, pain, and unwanted side effects will be conducted during follow-up visits, with regular evaluations of study participants held in collaboration with occupational therapists and researchers. If a patient scores ≥4 on DN4 and does not respond to conservative treatment for neuropathic pain (desensitization), he/she will be assessed by a hand surgeon for further diagnostics.

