## Trial design {8}

This is a single-center, unblinded, superiority, randomized controlled trial. The study includes patients with isolated digital nerve injuries, defined as a single digital nerve laceration without concomitant injury to flexor or extensor tendons, or to adjacent digital nerves. Patients will be randomized in a 1:1 ratio, without stratification, to either surgical nerve repair and cast, or immobilization only.

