### Participant timeline {13}

#### Sample size {14}

This study was designed as a prospective superiority trial, aiming to determine whether one treatment strategy resulted in a superior sensory recovery outcome compared to the other. The primary endpoint was the proportion of participants achieving recovery of sensibility, defined as S2PD ≤ 10 mm, measured at the 1-year follow-up.

A power calculation was performed based on the assumption of a 20% clinically meaningful difference between groups. Using a two-sided significance level of *p* < 0.05 and a statistical power of 80%, the required sample size was calculated to be 150 patients. This calculation was based on an expected outcome proportion derived from a previously published study [38]. To account for an anticipated dropout rate of 10%, the total sample size was adjusted to 166 participants.

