### Composition of the data monitoring committee, its role and reporting structure {21a}

This study does not have a data monitoring committee or a sponsor. It is a single-center, randomized controlled trial, and no data is stored outside the hospital. No external party has access to data.

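### The interim harm rule is purely relative: with 42 per arm it cannot trigger once the lower arm exceeds 8/42 (19.0%) or 10/42 (23.8%), yet it can trigger on counts as small as 4 v 1

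*Protocol article*

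**What the plan says.** The rule is in the protocol article, Interim analyses {21b}. The look takes place "Once 42 patients, representing half of the planned study population, in each group, have completed the 6-month follow-up". The event is binary: "A potential neuroma is considered present if a patient scores ≥4 on the DN4". The consequence is mandatory: if a ≥"400% difference is observed in the proportion of patients scoring ≥4 on the DN4 questionnaire between the treatment groups, the study will be terminated". The ground given is too high an incidence of neuropathic side effects.

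The section gives no minimum number of events, no absolute difference, and no test or interval. It does not name the reference arm or the direction, and it does not say what happens if one arm has no cases. The research team makes the assessment. The section on the data monitoring committee {21a} adds: "This study does not have a data monitoring committee or a sponsor". No expected rate of DN4 ≥4 is given anywhere in the article.

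**The concern.** This is the only numerical stopping boundary in the article, and its outcome is mandatory. A bare ratio of two small proportions behaves badly at both ends. When the event is common, the ratio is capped because no arm can exceed 100%, so a very large excess of harm may not meet the rule. When the event is rare, one or two patients can move the ratio past any threshold, so chance alone may end the trial. The phrase is also ambiguous: a 400% difference may mean four times the lower arm or 400% more than it, that is, five times. With no independent committee, the unblinded research team would have to settle these questions with the data in view.

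**Working it through.** **Inputs.** Total of 166 (Sample size {14}: "To account for an anticipated dropout rate of 10%, the total sample size was adjusted to 166 participants"); 1:1 allocation (Trial design {8}); 42 per arm and the ≥400% threshold (Interim analyses {21b}). The true DN4 ≥4 rates used in steps 4 and 5 are assumptions, because the article gives none.

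**1. The plan's own figure.** 166/2 = 83 per arm; 83/2 = 41.5, rounded up to 42. The stated 42 reproduces.

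**2. Scale and ceiling.** A difference of 400 percentage points is impossible, and a shortfall relative to the higher arm cannot exceed 100%. The rule must therefore be relative to the lower arm: stop if max(x, y) ≥ r × min(x, y), with r = 4 or 5 and x, y the counts out of 42. A trigger needs r × min ≤ 42.

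- r = 5: the largest lower-arm count is 8 (needs 40/42 in the other arm); 8/42 = 19.0%. With 9, the other arm would need 45 of 42.
- r = 4: the largest lower-arm count is 10 (needs 40/42); 10/42 = 23.8%. With 11, the other arm would need 44 of 42.

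So 11/42 v 42/42 (Fisher p about 1e-13) triggers neither reading. This step needs no assumed rate.

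**3. Smallest triggers.** With at least one case in each arm, these are 4 v 1 for r = 4 (two-sided Fisher p = 0.36) and 5 v 1 for r = 5 (p = 0.20). If a zero arm counts as an infinite ratio, 1 v 0 triggers (p = 1.0).

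**4. False stops with equal true rates.** P(stop) is the sum of b(x; 42, p) × b(y; 42, p) over all triggering pairs (x, y), in either direction, where b is the binomial probability.

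| Assumed common rate | r = 5, zero arm triggers | r = 5, never | r = 4, zero arm triggers | r = 4, never |
|---|---|---|---|---|
| 2% | 49% | 0.1% | 50% | 0.7% |
| 3% | 41% | 0.6% | 43% | 2.7% |
| 5% | 23% | 2.9% | 29% | 8.1% |
| 8% | 11% | 5.4% | 16% | 10.3% |
| 10% | 7% | 4.8% | 11% | 8.3% |

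Hand check at 2%: P(no cases in an arm) = 0.98^42 = 0.428. P(exactly one arm empty) = 2 × 0.428 × 0.572 = 0.490. Adding 0.001 for triggers without an empty arm gives 0.491. Nearly all of the 49% comes from the zero-arm convention. If only one direction counts, each figure halves (49% becomes 24.5%).

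**5. Stops under a true difference.** Same sum with unequal rates.

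| Assumed true rates | r = 5, zero arm triggers / never | r = 4, zero arm triggers / never | Two-sided Fisher at 0.05 |
|---|---|---|---|
| 3% v 15% | 58% / 30% | 67% / 39% | 32% |
| 5% v 25% | 56% / 44% | 68% / 57% | 68% |
| 10% v 40% | 38% / 37% | 55% / 53% | 87% |
| 20% v 60% | 11% / 11% | 24% / 24% | 96% |

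The last row is a 3-fold ratio, below either threshold. It shows which harms a ratio rule leaves out by construction, not a failure to meet its own target.

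**The case against.** Four objections have weight.

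- **Stopping on noise.** A reader might infer that the rule would end a sound trial about half the time when neuropathic pain is rare. The article does not support that. A percentage difference from zero is undefined, and the rule does not say that it triggers. If it never does, the false-stop chance at 2% to 5% lies between 0.1% and 8.1%. What stands is that the convention is missing and alone moves the 2% figure from about 50% to under 1%. The never-trigger convention has its own cost: 0 cases against any number in the other arm could then never stop the trial.
- **No protection when pain is common.** A reader might infer that participants would be left without safeguards. That goes too far. The Complications section provides further examination at DN4 ≥4. Interim analyses {21b} provides regular evaluation and hand-surgeon assessment of those who do not respond to conservative treatment. Adverse event reporting {22} provides a between-group comparison at the interim. None of these is a stopping boundary, so the ceiling stands.
- **A significance test is simply better.** The calculations do not show this. At 3% v 15%, Fisher's test detects less (32%) than the rule does when a zero arm triggers (58% or 67%). Requiring significance before a harm stop is a design preference.
- **Detail left to another document.** A separate analysis plan may exist. But the article states this boundary in full, and the access section {31c} presents the article as the complete protocol. The problem is the form of a stated rule, not an omission.

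**Conclusion.** The point holds in this form: a mandatory, ratio-only boundary at 42 per arm cannot trigger above 8/42 (5-times) or 10/42 (4-times) in the lower arm, whatever happens in the other arm, and it can trigger on 4 v 1 or 5 v 1. Both facts follow from the stated sample size and threshold alone. The 1 v 0 trigger holds only if a zero arm is read as an infinite ratio.

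The false-stop and detection probabilities rest on assumed DN4 ≥4 rates, independent binomial arms and stops in either direction. They should be read as a range across the two zero-arm conventions, not as one figure. The single look at a safety outcome does not of itself bias the primary estimate. What is at stake is whether the trial stops when it should, and only then.

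**What to change.** Amend the sentence in Interim analyses {21b} before the interim look:

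- Express the boundary as an absolute difference in the proportion with DN4 ≥4, of a size the investigators choose. This removes both the ceiling and the zero-arm problem.
- Pair it with a stated allowance for chance: either a minimum event count or an exact interval for the difference.
- State the direction or directions covered.
- State whether arms are compared as randomised or as treated, and reconcile this with the section on non-adherence and missing data {20c}, which assigns complications to an as-treated analysis.
- Report the chosen rule's false-stop and detection probabilities at 42 per arm over a range of assumed rates. No specific replacement has been evaluated here, so this has to be done for the rule actually adopted.

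The cost is one protocol amendment and a short calculation. The small downside is that the investigators must commit to an absolute difference now.

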### Methods for additional analyses (e.g. subgroup analyses) {20b}

The primary outcome will be analyzed with mixed models effects, taking possible confounders into account, such as age (years), gender (female/male), smoking (yes/no), handedness (left/right), injury mechanism, level of injury (proximal/middle phalanx), distance from injury to fingertip (mm), time from injury to operation/immobilization (days). No other additional or subgroup analyses are planned.

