### Outcomes {12}

#### Primary outcome

Primary outcome measures will be collected at 12 months after injury.

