### Static Two-Point Discrimination test (S2PD)

The primary outcome of this study is the return of sensation 12 months after nerve injury, assessed using the S2PD, measured in millimeters. S2PD is the most widely used test to evaluate sensory function in the fingers [7]. The S2PD test evaluates tactile spatial acuity i.e. the ability to distinguish between two separate points of contact on the skin. The S2PD test, initially described by Weber in 1834, and later modified by Moberg [7] is performed using the Mackinnon-Dellon Disk-Criminator™ by applying two pins longitudinally over the radial and ulnar sides of the fingertip, with distances ranging from 0 to 25 mm. The minimum distance at which an individual can accurately distinguish between one or two points is recorded as the S2PD value. The test will be conducted in a standardized manner, ensuring that the pins are applied with just enough pressure to cause skin blanching [8], as excessive force may stimulate other receptors rather than mechanoreceptors responsible for pressure sensation [9, 10]. The injured finger is examined, as well as the corresponding finger on the uninjured hand for comparison. A correct response in seven out of ten random applications is required for a valid measurement.

Classification of sensory recovery according to the Mackinnon-Dellon scale [11], modified from the Highet classification, will be used. Sensation is classified as: Poor = >15 mm, Good = 7–15 mm, Excellent = 2–6 mm. The test and its validity have been questioned [12, 13].

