### Other outcomes

#### Demographics

Data, including age (years), perceived gender (male/female), smoking (yes/no), handedness (right/left/ambidexter), occupation, comorbidities, injury mechanism, level of injury (middle or proximal phalanx), and time from injury to operation/immobilization (days), will be collected at inclusion.

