## Statistical methods

### Statistical methods for primary and secondary outcomes {20a}

Primary outcome is a dichotomous outcome that will be presented as proportions of patients obtaining return of 2PD < 10 mm 1 year after injury, presented with 95% confidence interval, and proportions between groups will be compared with Chi^2^ analysis.

All numerical values will be tested for normality by Shapiro–Wilk’s test.

We assume normality/parametric data for age, AROM, and grip strength. Results are presented as numerical values on an interval scale. Central tendencies of data will be described as means with their corresponding standard deviation, and comparisons between groups will be performed with Student’s *t*-test or repeated measures ANOVA.

Categorical data will be presented as proportions and compared by Chi^2^ analysis, unless Fisher’s exact test is demanded due to expected small numbers. Ordinal data will be presented as medians and interquartile range (IQR), and Mann–Whitney *U*-tests or Wilcoxon’s test used for comparisons between groups.

We assume a skewed distribution for time to injury, sick leave, and PROMs, which will be presented as medians with IQRs and compared by Mann–Whitney *U*-tests or Wilcoxon’s test.

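### The adjusted analysis in {20b} applies a mixed model to a primary outcome that is one yes/no value per patient at 12 months, with no grouping factor named

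*Protocol article*

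**What the plan says.** The statistical methods section {20a} sets the endpoint: "Primary outcome is a dichotomous outcome that will be presented as proportions of patients obtaining return of 2PD < 10 mm 1 year after injury". It also sets the primary test: "proportions between groups will be compared with Chi^2^ analysis". The sample size section {14} likewise uses a proportion at one time point: "The primary endpoint was the proportion of participants achieving recovery of sensibility, defined as S2PD ≤ 10 mm, measured at the 1-year follow-up". The outcomes section {12} fixes the timing: "Primary outcome measures will be collected at 12 months after injury".

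The design leaves no evident clustering. Section {8} states: "This is a single-center, unblinded, superiority, randomized controlled trial". Randomisation is unstratified, and the inclusion criteria admit one isolated digital nerve injury per patient.

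Section {20b} then announces the additional analysis: "The primary outcome will be analyzed with mixed models effects, taking possible confounders into account". Eight covariates are listed. No random effect, cluster, visit term or outcome scale is given, and the section adds that nothing further is planned. The S2PD outcome description in {12} puts the same outcome on another scale: "The primary outcome of this study is the return of sensation 12 months after nerve injury, assessed using the S2PD, measured in millimeters".

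**The concern.** A mixed model needs units that contribute several observations, or units that share a cluster. The primary outcome as defined supplies one binary observation per patient, and {20b} names no cluster. Two natural readings follow, and neither gives a clean adjusted version of the primary comparison.

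- **Patient random effect on the 12-month responder.** The between-patient variance cannot be separated from the binary sampling variation, so the reported odds ratio depends on a quantity that the data do not determine.
- **Repeated S2PD over the Table 1 visits.** The model can then be estimated, but it describes S2PD over follow-up. It addresses the 12-month question only if the model includes a 12-month contrast and that contrast is the one reported.

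This is the only adjusted analysis planned for the primary question in an unblinded trial. As worded, it leaves scale, visits and random effect open, and the adjusted estimate could differ from the chi-square result for reasons unrelated to covariate imbalance.

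**Working it through.** The plan gives no figure for this model, so there is none to reproduce. The check asks whether the stated model can be estimated on the stated endpoint.

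**Inputs.** One binary value per patient ({12}, {14}, {20a}); 150 evaluable patients ({14}) at 1:1 ({8}), so 75 per arm. The protocol does not state the expected proportions, so the counts below are assumptions: 38/75 (50.7%) v 53/75 (70.7%), a difference of 15/75 = 20 percentage points. Section {14} assumes a 20% difference without saying whether it is absolute or relative; absolute is assumed here.

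**Model.** logit P(Y = 1 | u) = a + b × arm + u, with u normal, mean 0, SD s, one u per patient. With one value per patient the likelihood depends only on the marginal probability in each arm, the average of expit(a + b × arm + u) over u. For any s, a and b can be rescaled so that these marginal probabilities equal the observed 38/75 and 53/75. The maximised log-likelihood is therefore the same for every s:

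38 ln(38/75) + 37 ln(37/75) + 53 ln(53/75) + 22 ln(22/75) = −97.3626

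**Fits with s held fixed (Gauss–Hermite quadrature).**

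| s | log-likelihood | b | odds ratio | Wald z |
|---|---|---|---|---|
| 0 | −97.3626 | 0.853 | 2.35 | 2.49 |
| 0.5 | −97.3626 | 0.900 | 2.46 | 2.49 |
| 1 | −97.3626 | 1.024 | 2.78 | 2.50 |
| 2 | −97.3626 | 1.391 | 4.02 | 2.50 |
| 3 | −97.3626 | 1.832 | 6.25 | 2.50 |

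The row s = 0 is ordinary logistic regression: (53 × 37)/(22 × 38) = 2.35. The data cannot choose between the rows.

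**Other assumed proportions.** With 48/75 (64%) v 63/75 (84%), the odds ratio runs from (63 × 27)/(12 × 48) = 2.95 at s = 0 to 9.19 at s = 3, again at equal likelihood.

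**Do covariates rescue it?** In 20 simulated data sets of 150 patients with arm and seven covariates (assumed coefficients), the log-likelihood over s = 0, 1, 2, 3 varied by 0.12 on average and by 0.36 at most. A 95% profile-likelihood limit for one parameter needs a drop of 3.84/2 = 1.92. The variance remains practically unidentified.

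**Repeated-visit reading.** Table 1 schedules S2PD at allocation, 3 weeks, 3, 6 and 12 months, so repeated data will exist. Sections {12}, {14} and {20a} nevertheless tie the primary outcome to 12 months or 1 year alone, and {20b} does not say that other visits enter the model.

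**The case against.** The strongest reply has four parts.

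1. **Detail may sit in an analysis plan that is not shown.** Random effects, link and time terms are commonly left there. This stands as far as missing detail goes, and no finding is made on that. What remains is that the stated model type does not fit the stated endpoint.
2. **A usable grouping factor may exist.** The Discussion refers to occupational therapists, in the plural, as assessors, and the intervention description allows surgeons of varying experience. A therapist random effect could be fitted to one binary value per patient. This stands as a possibility, so it would be wrong to say that no mixed model can be fitted. But {20b} names neither factor, and operating surgeons exist only in the surgical arm.
3. **A repeated-visit model can deliver the 12-month effect.** True, if it has arm-by-visit terms and the 12-month contrast is reported. A reader might infer that the plan swaps the endpoint for all visits, or averages the effect over them with a loss of power. The documents do not support this: {20b} neither brings in the earlier visits nor rules out an arm-by-visit term.
4. **Inference is barely affected.** A reader might also infer that the model would give a misleading standard error or test. The table above does not support that: z stays at about 2.5 for every SD. The harm is to the size and interpretation of the reported odds ratio.

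The analysis is also additional, not primary.

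**Conclusion.** The point holds in a limited form. Section {20b} assigns a mixed model to an outcome that the rest of the article defines as one yes/no value per patient at 12 months, and names nothing to group by. With a patient random effect, the variance is not identifiable and the conditional odds ratio is arbitrary: 2.35 to 6.25 on the same illustrative data for SDs of 0 to 3. That range rests on the assumed counts; the flat likelihood without covariates does not. With covariates, the near-flat result rests on the simulated settings.

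The primary analysis and the sample size are untouched. The consequence is confined to the only planned adjusted analysis of the primary question, which should be corrected but does not threaten the main result.

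A minor related mismatch: the demographics section collects handedness in three categories, including ambidexter, while the covariate list in {20b} shows two.

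**What to change.** In {20b}, replace the mixed-model wording with logistic regression of the 12-month responder, using the same responder definition as {20a}, on arm and the listed covariates that are fixed before randomisation. Report the adjusted effect with its 95% CI. Since {14} and {20a} differ on whether exactly 10 mm counts as recovery, one definition should serve throughout. Time from injury to operation or immobilisation needs care: treatment follows allocation, so this covariate is not fixed before randomisation.

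If a mixed model is wanted, label it a separate supportive analysis of S2PD in mm over visits, with arm, visit, arm-by-visit and a patient random effect, and report the 12-month contrast. Code handedness as collected.

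The cost is a wording change in the analysis section. No new data, patients or visits are needed, and with recruitment expected to run to the end of 2030 the change can be made well before the final analysis.

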### Exclusion criteria

Suspected concomitant tendon injury or fracture.Injury to the digital nerves in the thumb.Ongoing wound infection.Chronic neurological conditions.Cognitive disabilities and dementia.Ongoing drug or alcohol abuse.Injury > 7 days at examination

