### Intervention description {11a}

At first examination, eligibility criteria, demographics, and information regarding the injury and its extent (perceived gender, date of birth, smoking, dominant hand, injured hand, profession, date of injury, injury mechanism, injured finger, injured nerve (ulnar/radial), level of injury (proximal or middle phalanx)) will be registered. Clinical examination will include sensory evaluation with S2PD of both the injured and the contralateral finger, as well as measurement of the distance between the injury and the fingertip in millimeters. Participants will be randomized to either nerve repair and cast or cast immobilization alone.

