### Control group

Cast immobilization will be maintained for 3 weeks. The cast will be administered by a nurse on the day of allocation.

In both groups, immobilization will consist of a cast over the wrist, stabilizing the metacarpophalangeal (MCP) joints in flexion and the proximal interphalangeal (PIP) joints in extension. Fingertips are left exposed to allow for sensory relearning exercises. Adjacent uninjured fingers will be included in the cast depending on the injury site and surgeon’s preference.

The follow-up protocols will be identical for both groups. All participants will be referred to an occupational therapist specialized in nerve rehabilitation to initiate early sensory relearning within 0–4 days following inclusion in the study. At 3 weeks, the cast and sutures will be removed. At this time, the occupational therapist will evaluate finger movement, sensation, strength, and overall hand function using standardized assessments, including active range of motion (AROM), S2PD, Semmes–Weinstein monofilament test (SWM), temperature and sharp/dull discrimination, the Mini Sollerman test, grip strength using the Jamar dynamometer, and Key pinch strength using the Pinch gauge. Follow-up evaluations will be conducted at 3, 6, and 12 months after inclusion (Table 1).

**Table 1 Tab1:** COPS trial participant timeline

	Study period							
	Enrolment	Allocation	Post allocation/surgery					Close out
**Timepoint**	*-t*_*1*_	0	0–4 days	3 weeks	3 months	6 months	12 months	> 12 months

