## Data collection and management

### Plans for assessment and collection of outcomes {18a}

Data will be collected at inclusion and during follow-up visits at 0–4 days, 3 weeks, 3, 6, and 12 months from injury (Table 1). At the time of inclusion, written informed consent will be obtained, and the inclusion protocol, including inclusion and exclusion criteria as well as demographic data (age, gender, smoking habits, handedness, occupation, comorbidities, injury mechanism, level of injury, injured hand, injured finger, injured nerve, distance from injury to fingertip, and time from injury to treatment), will be completed. After consenting to participate, randomization will be carried out, and PROMs (Quick-DASH, HADS, HQ-8 (before operation), PCS) will be filled out. Sensory relearning is offered 0–4 days after injury. At 3 weeks, the cast and sutures will be removed by a nurse before seeing the occupational therapist. At follow-up visits, the investigating occupational therapist uses the follow-up study protocol for assessments (S2PD, AROM, SWM, Mini Sollerman test, Temperature sensation, Sharp/Dull, Grip strength + VAS, Pinch grip + VAS) and PROMs (Quick-DSAH, HQ-8 after operation/treatment, DN4), to make sure that all measurements and forms are completed.

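### The additional adjusted analysis of the primary outcome conditions on time from injury to treatment, which in the surgery arm is settled only after randomisation

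*Protocol article*

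**What the plan says.** All references are to the protocol article.

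- **Main analysis ({20a}).** The primary outcome is dichotomous, and "proportions between groups will be compared with Chi^2^ analysis". No covariates enter.
- **Additional analysis ({20b}).** "The primary outcome will be analyzed with mixed models effects, taking possible confounders into account". The examples listed include "time from injury to operation/immobilization (days".
- **Timing in the cast arm (Control group).** "The cast will be administered by a nurse on the day of allocation".
- **Timing in the surgery arm.** No section ties the operation to the day of allocation. The inclusion criteria require only that treatment or surgery be possible within 10 days of injury. The exclusion criteria remove "Injury > 7 days at examination", so a patient may be examined as late as day 7.
- **When the covariate is said to be known.** The Demographics section says "time from injury to operation/immobilization (days), will be collected at inclusion". Table 1, through its footnote, puts it among the demographics marked in the enrolment column. Section {18a} lists time from injury to treatment in the inclusion protocol, and then says "After consenting to participate, randomization will be carried out".

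**The concern.** A covariate in an adjusted comparison of randomised arms should be fixed before allocation. This one is fixed before allocation in neither a formal nor, for surgical patients, a practical sense: the date of the operation follows from having been allocated to an operation. For a given time to randomisation, a surgical patient's value can only equal or exceed that of a comparable cast patient, so randomisation does not balance it.

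Two things are at stake. First, the estimand. By naming the variable a possible confounder, the protocol supposes that it affects recovery. On that premise, any wait for surgery is part of what allocation to surgery brings, and conditioning on it takes that part out. The adjusted result then no longer compares the two strategies as randomised, although the protocol otherwise follows intention to treat. Second, precision: the covariate is correlated with arm, which inflates the standard error of the treatment effect.

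There is also an internal inconsistency. A value that depends on a later operation cannot be collected at inclusion.

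**Working it through.** **Is it post-randomisation?** Write T0 for days from injury to randomisation, G for days from randomisation to surgery, and A for arm (1 = surgery). Then T = T0 in the cast arm and T = T0 + G in the surgery arm, with G ≥ 0. Under the eligibility limits a patient examined on day 7 still has 10 − 7 = 3 days before the 10-day limit, and one examined earlier has more. The plan therefore allows G > 0 but gives no distribution for it. There is no printed figure to reproduce on this point, and what follows rests on assumed delays.

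**Precision.** Assumptions: T0 uniform on 0–7 days, G uniform on 0–d days, 1:1 allocation.

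- Between-arm variance of T = 0.25 × (d/2)²
- Within-arm variance of T = 7²/12 + ½ × d²/12
- R² = between / (between + within); VIF = 1/(1 − R²)
- Power for the arm effect = Φ((1.960 + 0.842)/√VIF − 1.960), starting from the protocol's 80% at two-sided 5%

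| d (days) | Between | Within | R² | VIF | 150/VIF | Power |
|---|---|---|---|---|---|---|
| 0 (same day) | 0 | 4.083 | 0 | 1.00 | 150 | 80% |
| 3 | 0.5625 | 4.458 | 0.11 | 1.13 | 133 | 75% |
| 5 | 1.5625 | 5.125 | 0.23 | 1.31 | 115 | 69% |
| 7 | 3.0625 | 6.125 | 0.33 | 1.50 | 100 | 63% |

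Simulation with T capped at day 10 agrees: R² 0.114, 0.235 and 0.338, VIF 1.13, 1.31 and 1.51. The loss is larger if patients are randomised sooner. With T0 uniform on 0–3 days and G uniform on 0–3, R² = 0.5625/(0.5625 + 0.75 + 0.375) = 0.33 and VIF = 1.50. The VIF formula is exact for a linear model and approximate for a logistic one. It ignores any precision gained from prognostic covariates.

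**Bias.** Assumptions: on the scale of proportions, surgery itself adds 0.20 and each day of delay lowers recovery by b. The effect of allocation is then 0.20 − b × mean(G), while the model that adjusts for T estimates 0.20.

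| b per day | Effect of allocation, mean G = 1.5 | Effect of allocation, G = 3 | Estimate adjusted for T |
|---|---|---|---|
| 0 | 0.200 | 0.200 | 0.20 |
| 0.01 | 0.185 | 0.170 | 0.20 |
| 0.02 | 0.170 | 0.140 | 0.20 |
| 0.03 | 0.155 | 0.110 | 0.20 |

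A large simulation of these scenarios, with T0 uniform on 0–7 days, gave the same pattern. At b = 0.02 the allocation effect was 0.171 (mean G 1.5) and 0.140 (G = 3), against 0.201 in both cases after adjusting for T. Adjusting for T0 instead returned the allocation effect to within 0.001 in every scenario, and T0 is independent of arm, so VIF = 1.00.

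If delay itself has no effect (b = 0) there is no bias, unless an unmeasured factor drives both the surgical delay and the outcome. One such simulated case gave a true 0.151 against an adjusted 0.162.

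**The case against.** The strongest reply is that this is an additional analysis. The prespecified comparison is the unadjusted chi-square test, and the covariate does not enter it. That stands: the main result, the sample size and the conduct of the trial are untouched.

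It is also fair to say that no section states when surgery takes place. The 10-day limit is an eligibility condition, not a scheduled wait. A reader might infer that treatment time differs between arms by design; the protocol permits a difference but does not impose one, and with same-day surgery the problem disappears. The size of the effect therefore cannot be read from the document.

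Other stronger readings are not supported either:

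- *The adjustment shrinks the estimated benefit of surgery.* Only precision is weakened. If delay is harmful, the estimate moves upwards.
- *The bias could double the effect.* That needs a chosen slope and a chosen direct effect, and the documents give neither.
- *A mixed model is impossible here.* Table 1 has S2PD at allocation, 3 weeks and 3, 6 and 12 months, so a patient-level random effect is available if the repeated visits are modelled. What is unclear is whether {20b} means that or the single 12-month binary value.
- *Leaving contralateral S2PD out of the model is an error.* It is measured ("Clinical examination will include sensory evaluation with S2PD of both the injured and the contralateral finger"), but the covariates in {20b} are given as examples, and choosing among prognostic covariates is a matter of judgement.

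What remains after these concessions is that the protocol names a variable settled after allocation as a confounder and describes it as known at inclusion. Neither statement is a detail that a later analysis plan would merely fill in.

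**Conclusion.** The point holds for the adjusted analysis in {20b} only. Time from injury to operation or immobilisation equals time to allocation in the cast arm and is settled after randomisation in the surgery arm. Adjusting for it removes any effect of waiting for surgery. When delay is harmful, the benefit of allocation to surgery is overstated by the daily loss times the mean gap: 3 points at 0.02 per day and 1.5 days, 6 points at 0.02 and 3 days, none if delay has no effect and shares no unmeasured cause with the outcome. With injury-to-randomisation time uniform over 0–7 days and surgical delays of 0–3 to 0–7 days, VIF is about 1.13 to 1.5, taking a nominal 80% power to about 75% to 63%. With same-day surgery there is no loss. All these sizes rest on assumed delays and slopes. The classification of the variable as collected at inclusion is wrong for surgical patients whatever the delays turn out to be, unless the operation precedes completion of the inclusion form, which the order of events in {18a} does not suggest. Severity: should-fix in a supporting analysis.

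**What to change.** - In {20b}, replace the covariate with time from injury to randomisation (inclusion).
- In the Demographics section, the Table 1 footnote and {18a}, stop describing time to treatment as collected at inclusion. Record it when treatment is given, and report it descriptively by arm.
- State whether the adjusted model targets the single 12-month binary outcome or the repeated visits. If the former, fit a logistic regression; a mixed model would need the repeated visits. An adjusted odds ratio is in any case a different quantity from the difference in proportions, so the two should not be expected to match.

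The cost is a sentence in {20b} and small wording changes elsewhere. The date of injury is listed under {11a}. A date of randomisation is not listed by name, but follow-up visits and sick leave are counted from inclusion, so that date should be on file; the trial team should confirm this. No new patient assessments are needed.
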